### 2.8. Study Outcome

The demographic information and the primary and secondary outcomes are collected and are listed in Table 1. Table 2 provides an overview of the primary and secondary indicators, including a description of the time points for each indicator.

### 2.9. Primary Objective

The primary endpoint of the study—the effect of esketamine versus sufentanil on the incidence of intraoperative hypoxemia—is the rate of SpO_2_ < 90 lasting for the 30 s during the bronchoscopy.

### 2.10. Secondary Objectives

Hemodynamic stability and safety (cardiovascular adverse events such as hypotension or bradycardia, which are measured as a change >25% from baseline and/or necessitating an intervention).

Time from end of bronchoscopy to Aldrete score of 9 (quality of awakening). This is defined as the time for a patient to return to full consciousness from sedation (Aldrete score of 9) after drug administration ceases, which should be accurate on a minute time scale).

Severe intraoperative hypoxemia (SpO_2_  <  75% at any time).

The total duration of intraoperative hypoxemia (total duration of SpO_2_ < 90%).

Incidence and score of PONV at the end of the operation and 1 day after the operation (Likert scale, classified as none, mild, moderate, and severe) [33].

Incidence of delirium within 3 days after bronchoscopy (to the evaluation of a patient’s delirium status and assessment by The Confusion Assessment Method (CAM)).

Incidence of postoperative fever.

Patient satisfaction (one day after the procedure patients will be visited to assess post-procedural satisfaction using the world SIVA International Sedation Task Force Tool [34]. (0 = very unsatisfied, 1 = unsatisfied, 2 = satisfied, 3 = very satisfied).

Propofol dosage in both groups.

The examination time.

The types of procedures.

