### 2.7. Anesthetic Management

Bronchoscopy is performed in the outpatient bronchoscopy room. All patients fast from food and water for 8 h before bronchoscopy. Preoxygenation is applied 5 min before anesthesia induction. General anesthesia is performed by anesthesiologists. All patients are monitored by noninvasive blood pressure, electrocardiography, and pulse oximetry and infused with 500 mL NaCl 0.9% at the rate of 250 mL/h. All patients receive oxygen administration (3–6 L/min via a nasal cannula) during the bronchoscopy. After preoxygenation with 100% oxygen, sufentanil (0.2 μg/kg) and propofol (1.5–2.5 mg/kg) are administered during the induction of anesthesia in the sufentanil group or propofol (1.5–2.5 mg/kg) and esketamine (0.2 mg/kg) in the esketamine group. Endoscopic examination starts after the patient has no obvious physical activity and the eyelash reflex has disappeared. Simultaneously, general anesthesia is maintained with propofol at a dose of 4–12 mg kg^−1^ h^−1^. The surgeon injects 5 mL of 2% lidocaine (Tianjin Jinyao Pharmaceutical Co., Tianjin, China) through the tracheoscope into the trachea after the tracheoscope enters the glottis. An amount of 0.5 mg/kg propofol will be added if the swallowing reflex, obvious body motion, or choking response is observed. For patients undergoing transient episodes of SpO_2_ below 90%, high fresh oxygen will be used first to obtain sufficient ventilation and to compensate for airway leaks. If this does not work, we will give the patient mandibular support. If none of these works, we will ask the performer to remove the placed bronchoscope and ventilate the patient for a few minutes until the SpO_2_ rises above 95% and then restart the procedure. In this study, it takes approximately 20 min to perform a bronchoscopy examination, and no additional muscle relaxants or tracheal intubation will be added. Intraoperative vasopressors will be administered to maintain mean arterial blood pressure within 20% of the baseline measurement. Propofol is discontinued at the end of the procedure.

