Heart rate (HR), SpO_2_, and noninvasive blood pressure (NIBP) are measured by an independent, blinded observer who collects research data at 3 min intervals. Patients are moved to the postanesthesia care unit (PACU) with oxygen support to maintain the oxygen saturation above 92%. Patients will be transferred to the PACU for Aldrete, delirium, and postoperative nausea and vomiting (PONV) assessment after awakening. The modified Aldrete score is used to assess the recovery from anesthesia and the return of psychotomotoric fitness. This validated assessment consists of 5 aspects (activity, respiration, blood pressure, consciousness, and SpO_2_), with a total score of 10. The clinical data on preoperative diagnosis, type of combined lung disease and blood gas, duration of bronchoscopy, and length of hospital stay are extracted from the medical record.

Safety will be assessed by interview and adverse event (AE) monitoring. All adverse events occurring during the whole study are recorded. Further follow-up is also necessary if there are clinical abnormalities.

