### 3.4. Secondary Outcome Analysis

For secondary outcome analyses, the χ^2^ test or the Fisher exact test will be used for categorical variables, including the incidence of intraoperative hypotension or bradycardia, severe intraoperative hypoxemia rate, PONV, delirium, or postoperative fever. The Student’s *t*-test or the nonparametric test will be used for the awakening time, the total duration of intraoperative hypoxemia, and patient satisfaction.

Two-sided *p* values < 0.05 will be considered statistically significant. All statistical analyses will be performed using SPSS Statistics 26.0 and GraphPad Prism 7.

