## Figures and Tables

**Figure 1 jcm-11-04587-f001:**
[figure not shown]
Study enrollment. SpO_2_, oxygen saturation; PONV, postoperative nausea and vomiting.

**Table 1 jcm-11-04587-t001:** Flow chart of the study. PACU, postanesthesia care unit; POD, postoperative day; CAM, the Confusion Assessment Method; PONV, postoperative nausea and vomiting. “×” means perfoming in that time.

Items	Visit 1	Visit 2	Visit 3	Visit 4	Visit 5
Time	One day before bronchoscoy	Morning of bronchoscopy	During bronchoscopy	PACU	POD1
Eligiblility screen	×				
Medical history and medication history	×				
Surgery history	×				
Physical examination	×				
Inclusion/exclusion criteria	×	×			
Informed consent		×			
Randomization		×			
Demographics			×	×	
Hemodynamic variables			×	×	
Study drug			×	×	
Outcome indicators			×	×	×
CAM				×	×
Aldrete				×	
PONV				×	×
Adverse events			×	×	×
Patient satisfaction					×

**Table 2 jcm-11-04587-t002:** Definitions of the multiple outcomes included in this study protocol. SpO_2_, oxygen saturation; PONV, postoperative nausea and vomiting.

Outcome	Definition	Instrumental/Tool
Incidence of intraoperative hypoxemia	The rate of SpO_2_ < 90% lasts for 30 s during the bronchoscopy.	SpO_2_
Hemodynamic stability and safety	Cardiovascular adverse events such as hypotension or bradycardia, which will be measured as a change >25% from baseline and/or necessitating an intervention.	Non-invasive blood pressure and electrocardiogram
Awakening time	Time from end of bronchoscopy to Aldrete score of 9.	Aldrete
Severe intraoperative hypoxemia	SpO_2_ < 75% at any time during the bronchoscopy.	SpO_2_
Total duration of intraoperative hypoxemia	Total duration of SpO_2_ < 90% during the bronchoscopy.	SpO_2_
PONV	The severity of PONV (none, mild, moderate, and severe).	Likert scale
Delirium	To evaluation of a patient’s delirium status within 3 days after bronchoscopy.	The Confusion Assessment Method
Adverse events	Accidental or adverse reactions to sedatives that threaten or cause patient injury or discomfort	World SIVA International Sedation Task Force Tool
Patient satisfaction	Patient satisfaction with the procedure experience (very unsatisfied, unsatisfied, satisfied, very satisfied)	Likert scale

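### Delirium is defined over 3 days after bronchoscopy, but the CAM is scheduled only in the PACU and on POD1, so a 3-day incidence would be unsupported and possibly understated

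*Protocol article*

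**What the plan says.** The outcome window is stated twice in the protocol article. Section 2.10 has "Incidence of delirium within 3 days after bronchoscopy", with the CAM as the instrument. Table 2 repeats it as "delirium status within 3 days after bronchoscopy". Section 2.8 says that Table 2 describes the time points of the outcomes.

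The assessments are set out in Table 1, which has five visits. The last two are the PACU (Visit 4) and POD1 (Visit 5). The CAM row is marked at these two visits only, and there is no column after POD1.

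Section 2.7 agrees with the first of these assessments: "Patients will be transferred to the PACU for Aldrete, delirium, and postoperative nausea and vomiting (PONV) assessment after awakening". It describes no later delirium assessment. Its only provision for later contact is conditional: "Further follow-up is also necessary if there are clinical abnormalities".

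Section 3.4 names delirium among the categorical outcomes to be compared between groups by the chi-square or Fisher exact test: "severe intraoperative hypoxemia rate, PONV, delirium, or postoperative fever".

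**The concern.** The outcome claims a period that the schedule does not cover. If the trial is run as Table 1 sets out, a patient who is CAM-negative in the PACU and on POD1 and becomes delirious on POD2 or POD3 is counted as free of delirium in a figure labelled as covering 3 days. Two things are at stake: whether the reported incidence matches its label, and how many events the comparison in Section 3.4 has to work with. Delirium is also named in the abstract among the data to be collected, and the background cites delirium reduction in children as a benefit of esketamine, so readers are likely to look at this result.

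**Working it through.** **Window against schedule.** The article states no delirium rate and no power for this outcome, so there is no figure to reproduce. The check is a comparison of places.

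| Place | What it fixes |
|---|---|
| Section 2.10 | delirium incidence over 3 days, by CAM |
| Table 2 | same window, same instrument |
| Table 1, CAM row | PACU and POD1 only |
| Table 1, last column | POD1 |
| Table 1, adverse-event row | during bronchoscopy, PACU, POD1 |
| Section 2.7 | delirium assessed in the PACU; later follow-up only if something abnormal is found |

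Of the three postoperative days in the window, one (POD1) has a scheduled CAM and 3 − 1 = 2 have none.

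**Is this only a detail left out of a condensed article?** No. Two statements in the article disagree. Other postoperative outcomes with a stated time fit Table 1: nausea and vomiting is defined at the end of the operation and the day after, and is marked at PACU and POD1; satisfaction is defined for the day after, and is marked at POD1. Delirium is the one outcome whose stated window runs past the last visit.

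**Effect on the incidence.** Let p be the true 3-day incidence and s the share of cases that first appear after the POD1 CAM. If none of those is picked up,

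observed incidence = p × (1 − s).

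Neither p nor s is in the documents. Purely as an illustration with assumed values:

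| s | p = 5% | p = 10% |
|---|---|---|
| 0% | 5% | 10% |
| 10% | 4.5% | 9% |
| 25% | 3.75% | 7.5% |
| 50% | 2.5% | 5% |

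The first row matters: if no delirium starts after POD1, the figure up to POD1 equals the 3-day figure.

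**Effect on the number of events.** With the planned 66 patients and an assumed p of 10%, the expected count is 66 × 0.10 = 6.6. With s = 25% it is 6.6 × 0.75 = 4.95. The outcome would have few events in any case, and the gap removes some of them.

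**Effect on the comparison.** Assume true rates of 10% and 5%.

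- Same share missed in both arms, s = 40%: the rates become 6% and 3%. The risk ratio stays at 2. The odds ratio moves from (0.10/0.90)/(0.05/0.95) = 2.11 to (0.06/0.94)/(0.03/0.97) = 2.06. The risk difference shrinks from 5 to 3 percentage points.
- Same absolute number of late cases in both arms, say 2 percentage points each: the rates become 8% and 3%. The risk ratio rises from 2 to 8/3 = 2.67.

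So the direction of any effect on the ratio depends on how late cases fall between the arms, which is unknown.

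**The case against.** The case on the other side is that the mismatch is small and that more can be read into it than the documents allow. Most of this stands, and it limits the point without removing it.

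- A reader might infer that the reported incidence must be wrong. That is not shown, because the figures coincide if no case begins after POD1.
- A reader might infer that late cases could not come to light at all, since "Bronchoscopy is performed in the outpatient bronchoscopy room". That describes the room, not the patients. Section 2.7 takes length of hospital stay from the medical record, so some may be inpatients, and it also provides for recording adverse events throughout the study and for follow-up of abnormalities. Late cases may therefore surface. But none of this is a scheduled CAM, and the adverse-event row of Table 1 also ends at POD1.
- A reader might infer that missing cases in both arms pulls the comparison towards no difference. The arithmetic above shows that this need not happen on the ratio scale.
- Two unassessed days out of three is a count of days, not of risk. It should not be read as two thirds of cases missed.
- The article does not show which side is the slip. Section 2.8 points to Table 2 for timing, and Table 2 says 3 days, so the visit table may be the part that is incomplete.
- Delirium is one of several secondary outcomes, and the repair may be wording only.

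What remains is that two stated parts of the plan disagree on when a tested outcome is measured, and no third part settles it.

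**Conclusion.** The point holds as an internal inconsistency in a secondary outcome. The definition covers 3 days, while the scheduled CAM covers the PACU and POD1 only. Under that schedule, onset after the POD1 assessment is not systematically detected, so a reported 3-day incidence would be unsupported and possibly understated, and the between-group test would have fewer events. The amount cannot be computed, because the documents give neither a delirium rate nor the timing of onset; the figures above rest on assumed values. No claim is made about the direction of bias in the risk ratio or odds ratio. The primary endpoint (intraoperative hypoxemia), its analysis and the sample size are untouched. It is worth correcting because the outcome is named and tested, and the correction can be made at almost no cost.

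**What to change.** Bring the outcome window and the visit schedule into agreement, in one of two ways.

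1. **Shorten the definition.** In Section 2.10 and Table 2, define the outcome as delirium by CAM in the PACU or on POD1, and drop the 3-day wording. Table 1 stays as it is. The cost is a change of wording; the downside is that the trial claims a shorter window.
2. **Keep the 3-day claim.** Add CAM assessments through POD3 to Table 1, and describe them in Section 2.7. The cost is further contacts for each of the 66 patients.

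The sponsor should say which was intended. Recruitment began on 9 March 2022, so if patients have already completed the schedule without a POD2 or POD3 CAM, the first option is the only one that applies to all patients alike. Under either option, the label on the reported result should match the assessments actually made.

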### 2.11. Sample Size Determination

Due to a lack of data from the literature, we were not able to estimate the differences between the three experimental conditions, which are necessary to calculate the sample size for a within-subject design. The sample size planned for this trial was based on the results of a pilot series preceding this research and on clinical judgment. The required sample size was calculated for the primary outcome and the incidence of perioperative hypoxemia. In our pre-experiment, the incidence of intraoperative hypoxemia was about 64% in the sufentanil group and 30% in the esketamine group. Given the 10% drop-out rate, the randomization of 33 individuals to each treatment group was required to achieve a level of significance and study power of 5% and 80%, respectively [35].

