## 2. Methods/Design

### 2.1. Trial Design

We prepared the study, including ethics approval and pilot testing, which lasted about 3 months. Formal subject recruitment began on 9 March 2022 and is anticipated to be completed by 30 August.

The study is being conducted in Beijing Chao-Yang Hospital, Capital Medical University. The study is designed as a prospective, randomized, controlled, single-trial that includes 66 patients undergoing flexible bronchoscopy and is reported following the Standard Protocol Items: Recommendations for Interventional Trials (SPIRIT) statement [31]. Ethics approval was obtained from the Ethics Committee of the Beijing Chao-Yang Hospital, Capital Medical University on 8 March 2022. The study will be performed following the Declaration of Helsinki [32] and is registered in the clinical trials (22 April 2022, 2022; Clinical Trial: ChiCTR2200058990). Written informed consent is obtained from all participants who meet the inclusion criteria. The present study meets the requirements of the Consolidated Standards for Trial Reporting (CONSORT) checklist. This study is based on a flowchart (Figure 1). Randomization is performed using the Randomization online version software (Table 1).

Potential participants undergoing bronchoscopy are screened for eligibility criteria. All enrolled patients are randomly divided into either the esketamine (Jiangsu Hengrui Pharmaceutical Co., Lianyungang, China) group or the sufentanil (Yichang Humanwell Pharmaceutical Co., Ltd., Yichang, China) group at a 1:1 ratio. We divide the patients into the esketamine group (receives esketamine/propofol sedation) or the sufentanil group (receives propofol/sufentanil sedation) during bronchoscopy. Standard deep sedation with propofol (Fresenius Kabi AB, [name]) target-controlled infusion (TCI) is provided by an anesthesiologist in both groups.

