### 2.5. Randomization and Blinding

Patients are randomly allocated to the esketamine group or the sufentanil group. A computer-generated randomization schedule is conducted to randomly assign included patients in a 1:1 ratio to reach double-blind treatment with either esketamine or sufentanil. Randomly permuted blocks are used for randomizing and are performed by a trained nurse who specializes in research. The nurse will utilize sealed opaque envelopes to reveal the treatment group on the morning of the operation. Esketamine and sufentanil are both colorless and transparent with 1 mL each. The esketamine or sufentanil is diluted to 10 mL with 0.9% saline by an anesthesia nurse on the day of bronchoscopy. The patients, anesthesiologists, investigators, those assessing the outcomes, and those analyzing the data are blind to the treatment assignment.

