### 3.2. Primary Outcome Analysis

The primary outcome of our analysis is the incidence of intraoperative hypoxemia. The comparisons in hypoxemia incidence between the two groups will be evaluated with an χ^2^ test, and 95% CIs will be calculated for the difference in hypoxemia incidence.

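### Section 2.11 claims 80% power with 33 randomised per arm and 10% drop-out; at about 30 evaluable per arm the planned chi-square test has about 77%

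*Protocol article*

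**What the plan says.** Protocol article, Section 2.11, takes its planning rates from a pilot: "the incidence of intraoperative hypoxemia was about 64% in the sufentanil group and 30% in the esketamine group". It then gives the sample size: "Given the 10% drop-out rate, the randomization of 33 individuals to each treatment group was required". The stated purpose of that number is "to achieve a level of significance and study power of 5% and 80%, respectively". The section names no formula and does not say how the drop-out allowance was applied.

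Section 3.2 names chi-square as the primary test, in the sentence that begins "The comparisons in hypoxemia incidence between the two groups will be evaluated with an". Section 3.4 sets the threshold: "Two-sided *p* values < 0.05 will be considered statistically significant". Section 2.5 says that the schedule will "randomly assign included patients in a 1:1 ratio", and Section 2.1 describes a "single-trial that includes 66 patients undergoing flexible bronchoscopy".

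Section 2.11 opens differently. It says the authors could not estimate "the differences between the three experimental conditions, which are necessary to calculate the sample size for a within-subject design".

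**The concern.** Section 2.11 presents 33 per arm as already allowing for 10% loss, so 80% should be the power with about 30 patients per arm in the analysis. The loss is part of the plan: Section 3.1 removes several categories of randomised patients from the final analysis, including sedation protocol violations and examinations that were not performed. If the planned test falls short of 80% at 30 per arm, the article overstates the trial's chance of detecting its own assumed effect.

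The opening sentence adds a separate problem. A reader who wants to check the calculation is told about three conditions compared within subjects, and nothing else in the article describes such a trial.

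**Working it through.** **Inputs.** p₁ = 0.64, p₂ = 0.30, difference 0.34, power 80%, drop-out 10% and 33 randomised per arm (Section 2.11); two-sided 5% (Section 3.4); chi-square test (Section 3.2); 1:1 allocation (Section 2.5). Evaluable per arm: 33 × 0.9 = 29.7, about 30.

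**Step 1: reproduce the 33.** Unpooled normal approximation:

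n = (1.960 + 0.842)² × (0.64 × 0.36 + 0.30 × 0.70) / 0.34² = 7.849 × 0.4404 / 0.1156 = 29.9, so 30 per arm.

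30 × 1.1 = 33. This is the stated figure.

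**Step 2: the drop-out allowance.** To keep 30 after 10% loss, one needs 30 / 0.9 = 33.3, so 34. Multiplying by 1.1 is one patient per arm short.

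**Step 3: the formula that matches the planned test.** The chi-square test uses the pooled variance under the null, with mean rate 0.47:

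n = [1.960 × √(2 × 0.47 × 0.53) + 0.842 × √0.4404]² / 0.34² = 32.6, so 33 **evaluable** per arm. With 10% loss, 33 / 0.9 = 36.7, so 37 randomised per arm.

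**Step 4: power at 30 evaluable per arm.**

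- Pooled approximation: Φ[(0.34 × √30 − 1.960 × 0.7058) / 0.6636] = Φ(0.722) = 76.5%.
- Unpooled approximation: Φ[0.34 × √30 / 0.6636 − 1.960] = Φ(0.846) = 80.1%.
- Exact, summing binomial probabilities over all tables with p < 0.05: 77.3% for the uncorrected chi-square test and 77.4% for the unpooled (Wald) test.

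The exact result for the Wald test settles whether this is only a choice of formula. The unpooled formula promises 80.1%, but the test that it describes delivers 77.4%.

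**Step 5: power of the chi-square test by number evaluable.**

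| Evaluable per arm | Pooled approximation | Exact |
|---|---|---|
| 30 | 76.5% | 77.3% |
| 31 | 77.9% | 79.6% |
| 32 | 79.2% | 81.7% |
| 33 | 80.5% | 83.6% |

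**Step 6: rounding of the pilot rates.** Let each rate move by ±0.5 point. At 30 per arm the pooled approximation then runs from 73.8% to 79.0%, and exact power from 74.8% to 79.8%. All of these values are below 80%.

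**Step 7: the design sentence.** Sections 2.1, 2.5 and 3.2 all describe two separate groups of patients, randomised 1:1 and compared with each other. The opening of Section 2.11 speaks of three conditions in the same subjects. The two descriptions cannot both be right.

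**The case against.** The strongest reply is that the 33 follows from its inputs by a standard formula, so nothing has been miscalculated. Section 2.11 names no formula, and the unpooled one is in common use. The rates are approximate and come from a pilot of unstated size, so a gap of about 3 points is small beside the uncertainty in the effect itself. Most of this stands: the figure is reproducible, the gap is small, and the ×1.1 allowance costs one patient per arm. What does not stand is that the gap is only a matter of formula. Exact power is about 77% for both the pooled and the unpooled test, and it stays below 80% over the rounding range.

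A reader might infer three stronger points that the article does not support:

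- **A much larger shortfall under Fisher's exact test or a continuity correction.** Section 3.2 fixes chi-square for the primary outcome. Fisher's test is named only for categorical data in Section 3.1 and for secondary outcomes in Section 3.4, and no continuity correction is mentioned. With 30 per arm and a mean rate of 47%, expected cell counts are about 14 to 16, so small counts would not force a change of test.
- **A sample size built on a three-condition, within-subject calculation.** Section 2.11 says that calculation could not be done, and then uses two-group pilot rates. The sentence is wrong for this trial but does not produce the 33.
- **An 80% that can be recovered simply by analysing everyone.** The exclusions in Section 3.1 would first have to change, and a patient whose examination was not performed has no intraoperative outcome to analyse.

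**Conclusion.** The point holds, and it is minor. With 64% versus 30%, a two-sided 5% chi-square test and about 30 evaluable per arm, power is about 77% (76.5% approximate, 77.3% exact) against the stated 80%. The type II error is therefore about 23% instead of 20%. Power reaches 80% only if almost nobody is lost: by exact calculation at 32 evaluable per arm, by the pooled approximation at 33. The result takes the pilot rates at face value, reads the 10% drop-out as loss from the analysis, and uses the uncorrected chi-square statistic. It does not undermine the trial. The three-condition, within-subject wording is a plain contradiction of the design and should be corrected at the same time, but it has no effect on the number.

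**What to change.** In Section 2.11:

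1. Replace the sentence on three conditions and a within-subject design with a description of the two-arm parallel comparison.
2. Name the sample-size formula and say how the 10% was added.
3. Restate the power, for example: *With 33 patients randomised per arm and 10% loss (about 30 evaluable), the two-sided 5% chi-square test has about 77% power for 64% versus 30%; with all 33 per arm analysed, power would be about 80% (pooled approximation) to 84% (exact).*

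The text should not promise that 80% will be reached, since that depends on the exclusions in Section 3.1. The cost is a few lines of wording and a slightly less favourable power figure. No extra patients are needed and the planned test does not change.
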